## Abstract

**Background:**

Stress is a widespread phenomenon and reality of everyday life, entailing negative consequences for physical and psychological wellbeing. Previous studies have indicated that exposure to greenspaces and nature-based interventions are promising approaches to reducing stress and promoting restoration. However, an increasing percentage of the population lives in urban regions with limited opportunities to spend time in greenspaces. In addition, urban settings typically feature increased levels of noise, which represents a major environmental stressor. Although various studies have compared the effects of exposure to greenspaces versus urban built environments, evidence of the effects of noise in this context is very limited. Psychophysiological benefits of exposure to greenspaces compared to urban built environments reported in earlier studies might be less (or at least not only) due to features of the greenspaces than to additional stressors, such as road traffic noise in the urban built environment. Hence, differences in the effects attributed to greenness in previous studies may also be due to potentially detrimental noise effects in comparison settings. This paper reports the study protocol for a randomized, controlled intervention study comparing the effects of walking in forest versus urban built environments, taking road traffic noise exposure during walks in the respective settings into account.

**Methods:**

The protocol envisages a field study employing a pretest–posttest design to compare the effects of 30-min walks in urban built environments and forests with different road traffic noise levels. Assessments will consist of self-reported measures, physiological data (salivary cortisol and skin conductance), an attention test, and noise, as well as greenness measurements. The outcomes will be restoration, stress, positive and negative affect, attention, rumination, and nature connectedness.

**Discussion:**

The results will inform about the restorative effect of walking in general, of exposure to different types of environments, and to different noise levels in these sites. The study will provide insights into the benefits of walking and nature-based interventions, taking into account the potential detrimental effects of noise exposure. It will thus facilitate a better understanding of low-threshold interventions to prevent stress and foster wellbeing.

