## Methods

### Study design

We will conduct a randomized, controlled intervention field study employing a pretest–posttest design to compare the effects of 30-min walks in urban built environments and forests with different road traffic noise levels. Healthy adults will be asked to go for a guided group walk with a maximum of six participants. The participants will be randomly assigned to one of the following conditions: urban built environment with high road traffic noise, urban built environment with low road traffic noise, forest with high road traffic noise, and forest with low road traffic noise. A fifth condition will be a walk in a forest with low traffic noise, in which participants walk with a mindfulness intervention. In this study protocol, we focus on the examination of the objective environmental factors, as noted above, and the last condition is not discussed here (above RF2). Data will be assessed before (t1) and directly after (t2) the walk. After this, participants will be instructed to walk individually three times during the subsequent 10 days. Ten days after participating in the field experiment, participants will receive an invitation to respond to a third questionnaire (t3). The third measurement point is only used for RF2 and is not included here; as for answering the research questions included in this study protocol, we focus only on measurement timepoints t1 and t2.

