### Procedures

The field experiment is based on a between-subject design, and assessments consist of self-report questionnaires, physiological measures, an attention test, and objective noise measurements. In preparation for the main data collection, a pretest was conducted in February and March 2022 to test the questionnaire and determine if changes in the experimental procedure were required. The questionnaire and experimental procedure were adjusted in line with the outcomes of the pretest.

Walking sessions will take place between 2:00 p.m. and 5:30 p.m., since participants’ salivary cortisol levels will be assessed, and salivary cortisol levels have been shown to fluctuate systematically during the day [60–62]. Additionally, stronger mental fatigue during the daytime is assumed [63] and hence, a higher need for restoration [64].

Before participation, individuals will be given a short introduction to the research topic, their task in the experiment, privacy policies, and asked to give their written informed consent. Before the date of participation, individuals will be asked to refrain from consuming caffeine and from performing exhausting physical activity 2 h before their walking appointment. Furthermore, participants will be requested to refrain from going for a walk on the day of their walking appointment before their participation and not to consume any drugs 24 h before taking the walk.

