In both models, we will specify fixed effects for conditions (vegetation and noise) and time (before and after the walk). Further, we will include an interaction term between vegetation and noise, as well as a random intercept term accounting for individual differences (one per subject). Additionally, in both models, the group constituting the experimental unit in this study will be entered as a second random intercept (one per group) to account for the hierarchical structure of the data due to the organization of participants into different groups. Since we will be conducting group walks, individuals will be subsamples of the walking groups, and the treatment will be applied to groups, not to individual participants. Therefore, the following model will be used: $$outcome \sim vegetation\times noise (1 |\mathrm{ group}/\mathrm{ subject})$$. If suitable, further exploratory models will be computed. For all analyses, we will set the significance level at .05 and analyses will be conducted with R [100] and R package lme4 [103].

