Third, it is important to note that without further information on the type of sound source, dB values possess only limited potential to predict noise annoyance and consequently stress. The assessed noise levels during the walks will partly reflect sound from individual motorized traffic but also other sound sources, such as sounds from people, animals, wind, and moving leaves from trees. The research team, with expertise in both environmental and health psychology as well as acoustics research, carefully discussed these limitations during the study design process; however, there is no viable way to fully avoid them in a field study. Therefore, we plan to account for this by extracting the percentage of time, during which road traffic noise is the dominant sound source in the sound measurements of every walk, as well as by including the *L*_Aeq_ during the time when road traffic noise is the dominating sound source as predictors for the statistical model. Fourth, especially when measuring sound during the walks in the forest settings, the sound of the experimenter walking partly masks other, quieter, or more distant sounds. Thus, the *L*_Aeq_ from such sounds (e.g., natural sounds) during the walks cannot be extracted from the recordings. However, because traffic noise is usually louder than the walking sound, this will only be a minor source of uncertainty regarding the recorded road traffic *L*_Aeq_ during the walks.

Finally, for individuals working full time, who could be hypothesized to be the ones with the highest stress levels, it might be difficult to find a convenient, appropriate, or suitable time slot, since walking sessions only take place in the afternoon.

The results of this study will inform us about the restorative effects of exposure to different types of landscape environments and to different road traffic noise levels at these sites. Through the methodology of this study, this research not only adds to the body of literature on the topic, but also provides an improved foundation for practical applications. The study will add information about the benefits of walking and nature-based interventions as well as their potential to reduce stress and promote wellbeing, thus facilitating a better understanding of low-threshold interventions to prevent stress and foster wellbeing. In addition, the results will have the potential to inform noise legislation and the implementation of spatial planning acts.

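### The abstract promises a result on the effect of walking itself, but every condition is a walk, so the pooled before–after change cannot be attributed to walking

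*Protocol article*

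**What the plan says.** The Discussion paragraph of the abstract opens with this statement: "The results will inform about the restorative effect of walking in general". Environment type and noise level follow as two further items, so walking itself comes first and stands apart from them. The main Discussion has a softer sentence: "The study will add information about the benefits of walking and nature-based interventions as well as their potential to reduce stress".

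Under Study design, participants are randomised between four conditions in scope. Three are described as "urban built environment with high road traffic noise, urban built environment with low road traffic noise, forest with high road traffic noise"; the remaining one is a quiet forest. A further mindfulness condition, outside the scope of this article, is also a forest walk. All are guided group walks, measured before (t1) and directly after (t2).

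Procedures describes a between-subject comparison and sets the afternoon time window because "salivary cortisol levels have been shown to fluctuate systematically during the day". Cortisol is sampled on arrival, directly before the walk and after it. The attention test is given before the walk and again afterwards.

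Data processing and statistical analysis says that in both models "we will specify fixed effects for conditions (vegetation and noise) and time (before and after the walk". It does not say how the time main effect will be read, and the model formula displayed there has no time term.

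**The concern.** An effect of walking in general means what walking does compared with not walking. Randomisation here allocates where and in what noise people walk, not whether they walk. The plan's only estimate on walking itself is therefore an uncontrolled before–after change.

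Two other contributors to that change can be found in the protocol. Cortisol is a primary outcome and is said to vary systematically over the day. The attention test is taken twice, so practice can alter the second score. Neither needs a walk.

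At stake is a conclusion with practical weight, since the protocol presents the study as informing low-threshold interventions against stress. A reader of the abstract would expect that conclusion to carry the authority of a randomised comparison, and it would not. The limitations in the main Discussion cover noise confounded with setting, noise variability, sound sources, masking by footsteps and availability of full-time workers. They do not mention the absence of a non-walking comparator.

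**Working it through.** The protocol gives no figure for this claim, so there is none to reproduce. The check is whether the design can identify a walking effect.

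**1. Inputs.** There are four conditions in scope and a fifth outside it, all walks (Study design). The number of conditions without a walk is 0. The comparison is between subjects (Procedures), and no non-walking period is described as a control.

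**2. Identifiability.** Let v = 1 for forest and n = 1 for low noise. Let S be the change over the session that would occur without a walk, assumed common to all arms. Let W be the effect of walking in the reference setting (urban, high noise). The mean change in an arm is

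Δ(v,n) = S + W + a·v + b·n + c·v·n.

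The four arms give four mean changes for five unknowns (S, W, a, b, c), and S and W appear only as a sum. With the baseline mean added, the design has 6 columns and rank 5. The mindfulness arm adds one equation and one new unknown, so it does not help. Adding a hypothetical no-walk arm, where the change is S alone, gives 6 columns and rank 6.

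In terms of what would be reported:
- Pooled change, arms equally weighted: S + W + a/2 + b/2 + c/4. S is included.
- Forest minus urban: a + c/2. S cancels.
- Low minus high noise: b + c/2. S cancels.

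**3. Illustration with the planning values.** Sample size calculation quotes restoration scores from an earlier study:
- Forest change: 5.16 − 4.60 = +0.56.
- Urban change: 4.20 − 4.56 = −0.36.
- Contrast: 0.56 − (−0.36) = 0.92.
- Pooled change: (0.56 − 0.36)/2 = +0.10.

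If S were +0.10, the changes due to walking would be +0.46 and −0.46. They average 0, and the contrast is still 0.92. The same data fit a positive or a zero average effect of walking, while the environment contrast does not move. These are another study's values and serve only to show the mechanism.

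**4. Cortisol, illustrative only.** The documents give no afternoon decline and no SD of change. Assume a natural fall of 5% to 10%, an SD of individual log-change of 0.3 to 0.4, and 70 participants (20 groups, the stated minimum, times an assumed 3.5 per group).
- SE treating people as independent: 0.3/√70 = 0.036; 0.4/√70 = 0.048.
- 10% fall: |ln 0.90| = 0.105, so z = 2.9 and 2.2.
- 5% fall: |ln 0.95| = 0.051, so z = 1.4 and 1.1.

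These figures ignore clustering, although the protocol treats the walking group as the experimental unit. With an assumed intracluster correlation of 0.1, the design effect is 1 + 2.5 × 0.1 = 1.25, and the 10% case becomes z = 2.6 and 2.0 (dividing by √1.25). With 0.2, the design effect is 1.5 and z = 2.4 and 1.8.

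**The case against.** The strongest reply is that the plan never sets out to analyse walking itself. RQ1 to RQ5 and H1 to H4 all concern differences between environments or noise levels. The analysis section compares change between conditions, and the sample size rests on the environment-by-time interaction. A pre–post mixed model needs a time term, and listing one is not a commitment to interpret it. The main Discussion's counterpart to the abstract sentence mentions only environments and noise. All of this stands. A reader might infer that the plan will report a significant time effect as a benefit of walking, but no section says so.

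It is also fair that aim 1 in Background and rationale can be served by a comparison of where people walk, and that the benefit sentence in the main Discussion can be read the same way. Aim 1 therefore needs no change.

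Some design features might seem to supply a control. The afternoon window limits variation between sessions but does not remove change within one. The two pre-walk cortisol samples give a short slope, but it mixes arrival and testing with the daily course, and no use of it is stated. The restoration scale asks how far the walk contributed, which is self-attribution and not a comparator.

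The cortisol figures are open to challenge. Every input is assumed, the 5% case is not significant, and the 10% case falls on either side of 1.96 once clustering is allowed for. A reader might infer from them that a false walking effect is likely. The documents do not support that.

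None of this rescues the abstract sentence. That the hypotheses do not address walking in general confirms that the abstract announces a conclusion the study is not built to reach. The point concerns a statement made in the article, and no separate analysis plan can supply the missing comparator.

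**Conclusion.** The point holds as a correction to one stated inference. The design identifies differences between settings and noise levels during walks. It does not identify the effect of walking, whatever the sample size. The rank result (5 of 6) assumes only that the no-walk trend is common to the arms. If the trend differed between arms, the walking effect would be no better identified.

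The reach is limited. It would be wrong to conclude that the randomised forest/urban or high/low-noise comparisons are compromised by this, since a common trend cancels from them. No hypothesis, model or sample size changes. The size of any bias in a pooled cortisol change cannot be stated from the documents, and the z-values above carry no weight in the conclusion.

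**What to change.** Three changes of wording:

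1. In the Discussion paragraph of the abstract, delete the reference to walking in general, leaving environments and noise levels.
2. In the abstract and the main Discussion, make clear that the benefits of walking are relative: forest against urban built settings, and low against high traffic noise, among people who all walk.
3. In Data processing and statistical analysis, state that the time main effect is a descriptive, uncontrolled before–after change and will not be interpreted as an effect of walking, because there is no non-walking condition.

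This needs no new arm, data or analysis. The cost is giving up one headline claim.

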**Trial registration:**

ISRCTN48943261; Registered 23.11.2023.

**Supplementary Information:**

The online version contains supplementary material available at 10.1186/s40359-024-01720-x.

## Background and rationale

Stress is a widespread phenomenon and part of our everyday life, with negative consequences for physical and psychological wellbeing. Data from the Swiss Health Survey 2017 revealed that in 2017, 21% of the respondents stated suffering from stress at their workplace “always” or “most of the time,” which represents an increase of 3% since 2012 [1]. Respondents who stated feeling stressed very often had a higher risk for burnout and emotional fatigue, compared with respondents reporting less stress [2]. Stress increases the risk of cardiovascular disease [3–7], gastrointestinal disorders [8], and blood pressure elevation [9]. Furthermore, stress is a risk factor for diabetes [10], obesity [11], and dementia [12] and is associated with hypertension [13]. Thus, stress constitutes an important public health issue, and research concerning stress recovery and approaches to prevent mental distress and improve psychophysiological wellbeing are needed.

In response to this urgency, some studies indicate that exposure to greenspaces can reduce stress symptoms and improve restoration and wellbeing [14–19]. Thus, exposure to greenspaces and nature-based interventions may be promising approaches to reduce stress and promote restoration. However, an increasing percentage of the population lives in urban regions with limited opportunities to spend time in greenspaces. In addition, such urban settings typically feature increased levels of transportation noise, representing a major environmental stressor and global challenge [20, 21]. Accordingly, the maintenance of environments suitable for promoting wellbeing, such as greenspaces, is suggested to foster mental health and support possibilities for coping with stress [22–31].

Much of the recent research on the benefits of engaging with greenspaces has been guided by theories concerned with psychophysiological stress reduction (stress reduction theory) [32, 33] or directed attention restoration (attention restoration theory) [34, 35]. Attention restoration theory states that nature allows restoration from a depleted capacity to direct attention, thus enabling more effective cognitive performance [35]; stress reduction theory proposes that natural environments promote recovery from stress and decrease arousal and negative thoughts through psychophysiological pathways [32, 33]. Correspondingly, there is an interest in measuring psychophysiological and attentional responses to greenspaces.

Although various earlier studies have compared the restorative effects of exposure to greenspaces versus urban built environments [18, 36–39], evidence of the effects of noise in this context is very limited. In their meta-analysis, Bowler and colleagues [36] compared the added benefits to health and well-being outcomes from activities such as walking and running in greenspaces versus synthetic (outdoor and indoor-built) environments. The results were mixed and revealed a paucity of good-quality studies. The authors concluded that well-designed studies are needed to further strengthen evidence and noted that differences between the benefits of greenspaces and urban built environments are less due to features of the greenspaces than to additional stressors in the urban built environment–one such stressor possibly being traffic noise. At the same time, Van Renterghem [31] discusses how vegetation can mitigate environmental noise perception, proposing a complex interplay between vegetation and noise factors for restoration.

In this context, we argue that although various earlier studies have compared the effects of exposure to greenspaces versus urban built environments, not enough attention has been given to potential confounding variables in previous studies. The greenspaces and urban built environments in earlier studies may have differed not only in terms of the extent of greenness of the compared environments, but also in terms of other variables. One particular variable in which environments might have differed is the extent of transportation noise (in particular road traffic noise) in different settings. Hence, differences in the effects attributed to greenness in previous studies may also be attributed to potentially detrimental (road traffic) noise effects in comparison settings, which potentially confounded previous results.

One previous study aimed at comparable noise levels in different environments, namely that by Gidlow and colleagues [40], who compared the effects of 30-min walks on stress, cognitive performance, restoration, and mood in a greenspace with water, a greenspace without water, and a pleasant residential urban environment. Differences between the different environments were found only for some of the outcome variables. The study showed no differences in the decrease in cortisol and improvements in mood between the different environments. A higher restorative experience in greenspaces, compared to the residential urban environment, and better cognitive performance 30 min after walking in greenspaces, compared to the residential urban environment, was shown. However, noise was only measured at one representative point on each route in each environment (urban residential 50.6 ± 4.3 dBA, green 47.5 ± 2.9 dBA, blue 45.6 ± 1.5 dBA) with two 15-min recordings in this study but was not assessed continuously during the walks. Furthermore, a difference of 5 dB between the conditions may result in a noticeable difference in noise levels between the different environments.

Research on noise exposure has shown associations between environmental noise, noise annoyance, and stress [41–45]. Studies on the effects of long-term noise exposure report an association between long-term aircraft noise exposure and a modified cortisol circadian rhythm [46] and decreased annoyance and increased wellbeing after a reduction of road traffic noise [47]. In contrast, various other studies could not establish such effects. Stockholm and colleagues [48] investigated the effects of long-term occupational noise on off-work cortisol levels. Their study showed no significant association between noise and cortisol levels. Other studies by Michaud et al. [49, 50] examined the effect of wind turbine noise levels up to 46 dBA on stress and found no effect. Studies on the effects of short-term noise exposure evidenced increased salivary cortisol levels for participants asked to solve a cognitive task in a louder (90 dBA) environment compared to a less noise-exposed environment (55–60 dBA, [51]; 45 dBA, [52]). Ellermeier et al. [44] found that skin conductance increased with the sound pressure level of vehicle sounds in a laboratory experiment. Overall, there is some evidence for stress as an effect of noise, suggesting that noise may also function as an acute impediment for stress reduction and restoration, but many results are based on cross-sectional data [41, 43, 53, 54] or laboratory studies [44, 51, 55–57]. Field experiments have shown weaker effects than laboratory research and have often relied on a very small sample size (e.g., Barbaresco et al. [58]). Good-quality field studies concerning the acute effects of noise on stress are lacking.

The planned study addresses this research gap. It will contribute to the existing literature with field experiments in ecologically valid settings, investigating the acute effects of walking in greenspaces versus urban built environments with different road traffic noise exposures, employing a longitudinal design. Following the need for robust experimental examination of psychophysiological responses to greenspaces expressed by Bowler et al. [36], the study presented in this protocol examines the effects of exposure to greenspaces versus urban built environments, with minimum confounding effects associated with road traffic noise. In addition, it provides a factorial design to study the individual contributions of environment and road traffic noise to the psychophysiological responses. It thus compares the effects of walking in greenspaces versus urban built environments with high versus low traffic noise exposure.

The overarching aim of this study is to assess the restorative effect of exposure to different types of environments (forests and urban built) and to different road traffic noise levels in these sites (high and low traffic noise), thus providing an improved empirical foundation for: (1) the practical application of walking and nature-based interventions as low-threshold approaches for stress reduction and the promotion of wellbeing; (2) the effects of additional environmental qualities of greenspaces and urban built areas like noise as an impediment to recover from stress; and (3) urban planning and the construction and preservation of restorative environments that support the wellbeing of inhabitants. In this paper, the study protocol is presented, and we used the SPIRIT checklist when writing our report [59].

The planned study is embedded in the research project RESTORE (Restorative potential of green spaces in noise-polluted environments). The purpose of the RESTORE project is to study green spaces as facilitators for restoration and stress recovery, as well as road traffic noise as an impediment to recovering from stress. The study presented here is the basis of a dissertation project examining the acute psychophysiological effects of walking in different environments and with disparate inner attitudes. In addition to investigating how much individuals restore, depending on *where* they go for a walk (research focus 1, RF1; focus of this study protocol), the study also investigates the effects of *how* individuals go for a walk and which inner attitude they adopt while walking. Specifically, this dissertation project examines whether helping people be more mindful while walking in forests may increase the potential positive effects of walking in forests on restoration (research focus 2, RF2). The current study protocol, however, focuses on describing the planned experiment for RF1). First, by means of inspecting the effects of 30-min walks, we will examine whether walking in forest settings, compared to walking in urban built settings, leads to a stronger increase in stress reduction, restoration, positive affect, attention, nature connectedness, and rumination as well as a stronger decrease in negative affect. Second, we will assess whether walking in an environment with less road traffic noise, compared to walking in an environment with more road traffic noise, increases the above effects.

